### Intervention

The study is pragmatic and assesses the effect of the treatment the clinician finds indicated, rather than a standard treatment. Therefore the study does not investigate a specific manual treatment, but investigates the whole chiropractic intervention with individual attention to the children’s potential biomechanical dysfunctions, as described below.

All children attend the chiropractor clinic two times a week for two weeks. After the fourth visit the parents continue their registration in the diary as an ‘after registration’ for at least three days, and fill out the final questionnaire including questions regarding the status of their child’s colic, bowel movements, burps, regurgitation and their belief regarding group allocation (Additional file 7). Hereafter an information visit takes place at the chiropractic clinic, where the parents hand in the completed diary and questionnaire and are informed whether their child has been in the treatment or control group. Children in the control group are then offered a similar treatment free of charge as the intervention group, if symptoms have not subsided, a strategy to improve adherence to the study.

#### The control group receives

Medical historyExamination without motion palpation of the joints, as this could approach mobilization. Examination includes undressing the child and observing if there are notable asymmetries of limb orientation and development, and distortions of the head, spine and body shape that could indicate a biomechanical dysfunction (related to muscles, ligaments and/or joints). Furthermore, the examination includes a mental and neurological statusBased on the medical history and examination the clinician estimates whether the child’s symptoms are likely to be related to a biomechanical dysfunctionPragmatic advice such as cycling with the child’s legs and changing the position of the child’s head from one nap to the nextAt the last visit, the chiropractor assesses if the child possibly can benefit from a similar treatment as given in the intervention group.

#### The intervention group receives

Medical historyFull examination, including motion palpation of the joints. To diagnose a biomechanical dysfunction examination includes static and movement palpation, observation of notable asymmetries of limb orientation and development, and distortions of the head, spine and body shape as well as exploration of muscular and ligamentous tonus and movement restrictions in articulations. Furthermore, mental and neurological status.Based on the medical history and examination the clinician estimates whether the child’s symptoms are likely to be related to a biomechanical dysfunction. This assessment is done before motion palpation of the joints and reassessed again after the motion palpation.Manual treatment will include manipulation or mobilization of the spine and/or the extremities as indicated by the child’s potential biomechanical dysfunctions, including movement restriction, tenderness or an obvious asymmetry in the muscles or joints. If no biomechanical dysfunction is detected mobilization is carried out where all the joints in the spine are lead through their normal range of movement.Specific advice directed towards any biomechanical dysfunction, and exercises that supports the effect of the manual treatmentAt the last visit the chiropractor assesses if the child’s course of treatment is completed or whether continued treatment is indicated

The manual therapy in the intervention group is thus administered when there is biomechanical dysfunction in one or more joints which the treating clinician relates to the child’s symptoms. In general, the treatment technique for restricted movements in joints in this age group is a very light short-term pressure with fingertips and gentle massage in case of hypertonic muscles.

The frequency and content of treatments is intended to resemble pragmatic daily clinical practice in order to optimize the treatments by individualization and to make the results generalizable.

### Outcome measures

The primary outcome measure is change in daily hours of crying (inconsolable crying and the time the child needs to be held and rocked to limit crying) based on the parental diaries (before and after treatment).

Secondary outcomes are based on information from parental diaries and the final questionnaire filled out by the parents and will include:Sleeping hours per day (change in mean daily hours of sleeping before and after treatment)Awake and content (change in mean daily hours of an awake and content baby before and after treatment)General Perceived Effect (colic has stopped/decreased/unchanged/increased)Bowel movements (more often/more rarely; easier/more difficult)Burps (easier/more difficult)Regurgitation (more/less)

#### Potential clinical predictors

Musculoskeletal problems as based on information from interview-based questionnaires and the chiropractors’ examination defined by favorite side during feeding or sleep, does not want to lie in abdominal position, difficulties dressing/undressing the child, objective signs as asymmetric gluteal folds/hips/knees/tonus in back musculature or skew position/C-curve and dichotomized into yes/noFactors related to pregnancy or birth e.g. complications related to pregnancy, induction of labor, duration of birth and different stages in birth, abnormal presentation in birth canal, interventions in birth such as vacuum assisted delivery and cesarean. This information will be drawn from interview-based questionnaires and supplemented if needed from hospital records and dichotomized into yes/no or categorized into appropriate categories.

Potential confounders include parental highest attained education, cohabitation status, smoking status of parents, birthweight, siblings with history of colic, stress in everyday life, severe stress related episodes during pregnancy or birth (e.g. severe illness or death among family members or close friends), mental illness of mother (e.g. depression). This information is obtained from the interview-based questionnaires. Other potential confounders are age and treating chiropractor which is accounted for in the stratified block randomization.

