**Fig. 1 Fig1:**
[figure not shown]
Study flow chart and time lime for participants

#### Visit 1

At the first visit, the PI, who is a medical doctor, assesses the child for eligibility and provides oral and written information (Additional file 2) regarding the project.

At the first visit the PI furthermore completes an interview-based questionnaire (Additional file 3) with the purpose to collect information about baseline variables and potential clinical predictors and confounders. The choice of variables was based on knowledge from existing literature [6–8, 19–21, 23, 27, 32] and focus group discussions with chiropractors and health visitors. Questions concerns the child’s crying pattern, birth weight and length, current weight and length, feeding mode and pattern, burps, regurgitation, bowel movements, anamnestic and objective signs of musculoskeletal problems (e.g. favorite side), previous treatment of the colic or other condition/disease, the mother’s health and use of medication, the parents’ level of serious mental stress during pregnancy and after the birth, mental stress of the parents in everyday life, educational level and cohabitation status of the parents, smoking status of the parents, siblings with history of colic, the parents’ belief regarding the effect of chiropractic treatment on colic, and selected factors related to pregnancy and birth. With consent of the parents pregnancy and birth related factors will also be collected in the mother’s hospital record, e.g. mother diagnosed with depression, gestational age at birth, durations of the different stages in birth, abnormal presentation in the birth canal and interventions in birth.

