If the parents’ consent to participate with their child (Additional file 4), they are introduced to a diary for use during the study (Additional file 5). This diary represents the parents’ structured notes of the child’s behavior, a validated method that has proved to be reliable as an objective recording of the child’s behavior and symptoms [33]. The parents are thoroughly instructed to record the child’s behavior throughout every 24 h during the whole project period. ‘Time rulers’ representing every 24 h divided in time intervals of fifteen minutes are filled out with different symbols representing the child’s behavior, including the amount of inconsolable crying (crying without an obvious reason that cannot be comforted by any attempt of the parents), the time the child needs to be held and rocked to limit crying (crying without no obvious reason that is only partly and briefly limited if the child is constantly held/rocked), the time the child is awake and content, and the time spent sleeping, feeding patterns and bowel movements. Consolable crying with an obvious reason that is easily comforted as e.g. hunger or a soiled diaper is registered as ‘awake and content’. To limit recall bias and make the registration as precise as possible the parents are advised to fill in the diary several times a day. Baseline registration of the crying pattern is done for at least three days whereupon a second visit from the PI is scheduled.

#### Visit 2

At the second visit, any difficulties filling out the daily diary is identified and the parents’ assessment of the crying pattern is evaluated in a second interview-based questionnaire (Additional file 6). Eligible children are then randomized, and an appointment is booked in one of the participating chiropractic clinics (parents’ choice). Four chiropractic clinics with seven chiropractors participate in the study, and all the chiropractors have a special interest and experience in pediatric practice. The treating chiropractors have been working from nine years to more than thirty years in the field.

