### Randomization and blinding

The allocation occurs through a 1:1 ratio by a predetermined restricted randomization scheme. The participants are stratified according to their age at enrollment (2–6 weeks; 7–10 weeks; 11–14 weeks) and the treating chiropractor. The eligible participants are randomly assigned in blocks of 4 to 6, according to computer-generated random numbers, to be enrolled in either the intervention or control group.

The computer generated block randomization was administered by a research assistant, not otherwise involved in the outcome measurements or the intervention. The research assistant then wrote the consecutive letters A and B on separate pieces of paper and then placed them in sealed opaque envelopes, which were given to each chiropractor. To take the above mentioned stratification into account the procedure was repeated and a different list of group allocation was made for each age level and each chiropractor in the study. When a child is randomized and an appointment booked, the PI informs the clinic of the next randomization number for that specific chiropractor and age group (which is a coded number not revealing group allocation). Only the chiropractor has the list that reveals if that certain randomization number means allocation to intervention or control group.

Hence, the intervention in this trial makes blinding of care providers impossible. The parents are blinded to their child’s allocation group during the project period. To uphold blinding of the randomization, all parents leave the chiropractor’s consultation room for a few minutes after history taking and examination, while the treatment is (or is not) carried out. For the analyses, the coding of intervention and control groups will be concealed from the PI and the statisticians performing the analyses. The randomization code will not be broken until the analyses are completed.

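### The musculoskeletal subgroup flag rests partly on an unblinded, post-randomization examination that differs by arm, so membership cannot be assumed independent of allocation

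*Protocol article*

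**What the plan says.** All references are to the Protocol article.

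- **Definition.** Potential clinical predictors defines the subgroup as "Musculoskeletal problems as based on information from interview-based questionnaires and the chiropractors’ examination". It lists history items (preferred side, dislike of lying prone, trouble dressing), visible asymmetries and back-muscle tone, and reduces them to yes/no.
- **Timing.** Under Visit 2, "Eligible children are then randomized, and an appointment is booked in one of the participating chiropractic clinics". The chiropractor first examines the child after that.
- **Examiner.** Randomization and blinding states that "Only the chiropractor has the list that reveals if that certain randomization number means allocation to intervention or control group" and that "the intervention in this trial makes blinding of care providers impossible".
- **Control-arm examination.** It is done "without motion palpation of the joints, as this could approach mobilization". It includes a medical history, observation of asymmetries and body shape, and a mental and neurological status.
- **Intervention-arm examination.** It adds static and movement palpation and "exploration of muscular and ligamentous tonus and movement restrictions in articulations". On the clinician's judgement of whether symptoms relate to a biomechanical dysfunction, it adds: "This assessment is done before motion palpation of the joints and reassessed again after the motion palpation".
- **Pre-randomization source.** At Visit 1 the primary investigator already collects "anamnestic and objective signs of musculoskeletal problems (e.g. favorite side" being the example given.
- **Use.** Statistical analyses repeats all analyses stratified by presence of musculoskeletal problems and calls this exploratory.

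**The concern.** A subgroup comparison keeps the protection of randomization only if membership does not depend on the arm. Here one of the two sources of the flag can depend on the arm in two ways: the examination procedure differs, and the examiner knows the allocation. If one arm's examination labels children differently, flagged children in the two arms differ in make-up, and so do unflagged children. Where that make-up is related to how crying changes over two weeks, a difference between arms appears within strata without any treatment effect.

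At stake is a stated aim. The Abstract and Background both say the trial will explore whether these children benefit more. The Discussion counts subgroup analysis among four main strengths, and says a confirmed subgroup finding could point to a causal relation and form the basis for stratified care.

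**Working it through.** **Step 1. Which parts of the flag can depend on the arm?**

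| Defining item | Control arm | Intervention arm |
|---|---|---|
| History items | interview, medical history | interview, medical history |
| Visible asymmetry, body shape | observation listed | observation listed |
| Back-muscle tone | not listed; a neurological status is done, content not stated | exploration of tone listed |

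Most items can be obtained in both arms. Tone is the one with a component named for one arm only. For every item taken from the chiropractor, the examiner is unblinded. The content of the examination itself depends on allocation, so the chiropractor must know the arm by the time it is carried out. The article does not restrict the flag to Visit 1 data.

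**Step 2. The plan's own figure, for scale.** The plan gives no figure on this point. Its sample size sets the yardstick: difference 1 h, SD 2.5 h, alpha 0.05 (two-sided assumed), power 80%. Per arm, n = 2 × (1.96 + 0.84)² × 2.5² / 1² ≈ 98.1, so 99. The t-based value is 99.08, so 100 per arm and 200 in total, as stated.

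**Step 3. Illustration with no treatment effect.** All inputs here are assumptions. Let p be the true prevalence, Se and Sp the flag's sensitivity and specificity in an arm, and d the number of hours by which truly affected children improve less.

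- Share flagged: F = p·Se + (1 − p)(1 − Sp)
- Truly affected among flagged: A = p·Se / F
- Truly affected among unflagged: B = p(1 − Se) / (1 − F)
- Spurious difference (intervention minus control): d(A_control − A_intervention) if flagged, d(B_control − B_intervention) if unflagged
- Subgroup contrast: flagged minus unflagged

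Worked case: p = 0.5, control Se/Sp 0.60/0.90, intervention 0.90/0.70, d = 1.

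- Control: F = 0.30 + 0.05 = 0.35; A = 0.30/0.35 = 0.857; B = 0.20/0.65 = 0.308
- Intervention: F = 0.45 + 0.15 = 0.60; A = 0.45/0.60 = 0.750; B = 0.05/0.40 = 0.125
- Flagged: 0.857 − 0.750 = +0.11 h. Unflagged: 0.308 − 0.125 = +0.18 h. Contrast: −0.08 h.

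All cases, in h/day, shown as d = 1 / d = 2:

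| p | Control Se/Sp | Intervention Se/Sp | Flagged, control vs intervention | Flagged stratum | Unflagged stratum | Contrast |
|---|---|---|---|---|---|---|
| 0.3 | 0.60/0.90 | 0.90/0.90 | 25% vs 34% | −0.07 / −0.15 | +0.11 / +0.23 | −0.19 / −0.38 |
| 0.3 | 0.60/0.90 | 0.90/0.70 | 25% vs 48% | +0.16 / +0.32 | +0.10 / +0.20 | +0.06 / +0.11 |
| 0.3 | 0.70/0.90 | 0.85/0.80 | 28% vs 39.5% | +0.10 / +0.21 | +0.05 / +0.10 | +0.05 / +0.11 |
| 0.5 | 0.60/0.90 | 0.90/0.90 | 35% vs 50% | −0.04 / −0.09 | +0.21 / +0.42 | −0.25 / −0.50 |
| 0.5 | 0.60/0.90 | 0.90/0.70 | 35% vs 60% | +0.11 / +0.21 | +0.18 / +0.37 | −0.08 / −0.15 |
| 0.5 | 0.70/0.90 | 0.85/0.80 | 40% vs 52.5% | +0.07 / +0.13 | +0.09 / +0.18 | −0.03 / −0.05 |
| 0.3 or 0.5 | 0.80/0.90 | 0.80/0.90 | equal | 0 | 0 | 0 |

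The last row shows that imperfect accuracy alone does no harm under no treatment effect. The harm comes from accuracy that differs by arm.

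**Step 4. Against sampling error.** Take the case with the largest contrast (35 vs 50 flagged and 65 vs 50 unflagged of 100 per arm) and use SD 2.5 h within strata.

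- SE flagged: 2.5 × √(1/35 + 1/50) = 0.55 h
- SE unflagged: 2.5 × √(1/65 + 1/50) = 0.47 h
- SE contrast: √(0.55² + 0.47²) = 0.72 h

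The largest spurious contrast, −0.50 h, is about 0.7 standard errors.

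**The case against.** The strongest reply is that most defining items are history or visible signs that both arms can supply, that the analysis is declared exploratory and meant to inform future studies, and that the artefact is smaller than one standard error even under unfavourable assumptions. All of this stands, and it limits the severity. It does not remove the point. The exploratory label addresses multiplicity and low power, not a bias built into the definition, and a larger sample would not shrink that bias.

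A reader might infer more than the text supports:

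- *That controls are only observed.* They also get a medical history and a mental and neurological status. Tone is absent from their list but not shown to go unassessed.
- *That signs will be found more often in the intervention arm.* This is plausible but not established. It depends on how far the flag rests on examination items, which the article does not say.
- *That the reassessment after palpation feeds the flag.* It concerns the clinician's judgement about biomechanical dysfunction, which is not among the defining items. Motion palpation findings and movement restriction are not among them either.
- *That palpation data would show the blinded analysts which group is which.* Nothing describes what the analysis dataset contains.
- *That the strata are necessarily biased.* With no treatment effect, bias arises only if the flag is prognostic.

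**Conclusion.** The point holds in a limited form. The flag draws partly on an examination that is post-randomization, unblinded and more extensive in the intervention arm, and one defining item matches a component listed for that arm alone. Membership cannot be assumed independent of arm. If the flag is prognostic, the stratified comparisons may be biased.

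Size and direction cannot be predicted. Under the assumed inputs, the spurious difference is −0.15 to +0.32 h/day in the flagged stratum and +0.05 to +0.42 h/day in the unflagged stratum. The contrast is −0.50 to +0.11 h/day, so it could hide or mimic effect modification.

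Severity is moderate. It might be tempting to call this a defect that must be fixed before the trial can be interpreted, but the primary comparison does not use the flag and the subgroup analysis is exploratory. It deserves correction because it is a stated aim and is offered as a possible basis for stratified care.

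**What to change.** Define the flag for the stratified analyses only from the history items and objective signs that the primary investigator records at Visit 1, before randomization, in every child. Fix this in writing before the randomization code is broken. Recruitment is still ongoing according to Trial status, so this can be done credibly.

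Do not use chiropractor examination findings to form the strata. Report them descriptively. At most, use the observational items listed for both arms in a sensitivity analysis labelled as post-randomization and unblinded. Having the chiropractor record an estimate before learning the allocation is not a good substitute: it would be a new clinic procedure and could not be applied to children already seen.

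The cost is mainly wording; the sample size does not change and no new data are needed. Signs found only at the chiropractor's examination no longer count, and the usable objective signs are limited to those on the Visit 1 form. That form (Additional file 3) is not shown, so its list of signs has to be checked first.

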### Sample size

Based on data from the pilot study we observed a mean reduction in hours of crying in the control group of 2.5 h per day before and after treatment with a standard deviation of 2.5 h. Based on group discussions in the research group to obtain a clinically satisfactory result, we therefore wish that children in the intervention group will have a reduction of one additional hour, resulting in a reduction of 3.5 crying hours. With an assumption of a common standard deviation of 2.5, a level of significance on 0.05 and a power of 80%, this result in a sample size of 200 children distributed with 100 in each group.

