### Statistical analyses

For the primary analyses the main endpoint is change in mean number of hours/24 h spent with excessive crying before and after the two weeks treatment period, comparing treated and not treated children (mean difference in hours of crying with standard deviations and *p*-value for difference between the groups using a two-sample t-test). Change in mean hours before and after equals 3–4 days before treatment and 3–4 days after treatment. All analyses will be performed by intention-to-treat principles and no data will be imputed.

To evaluate the independent effect of treatment, multiple linear regression analyses of the change in crying hours will be performed including baseline values of the crying hours, randomization group and stratification factors as independent variables.

Secondary outcomes will be analyzed similarly. Furthermore, a secondary repeated measures linear regression analysis will evaluate change over time with regard to time spent crying, sleeping, and time being awake and content.

In a secondary explorative analysis it will be evaluated if subgroups of children with suspected musculoskeletal problems will benefit more from the intervention than others, and all analyses will be repeated stratified for presence of musculoskeletal problems. This hypothesis is based on the theory that the children cry because of pain that origins from the musculoskeletal system [27]. Furthermore, existing literature suggest there may be a relationship between complicated births and infantile colic [20, 34], and one theory is that complicated births may induce musculoskeletal problems [23, 27]. We therefore hypothesized that a potential beneficial treatment effect of chiropractic care may be greater for the children born by a complicated birth when compared to the children born at an uncomplicated birth. Therefore, similarly to presence of musculoskeletal problems, analyses will be repeated stratified for elected factors related to birth. These analyses will be explorative in nature, but could help to identify potential clinical predictors of treatment effects to be incorporated in future studies. Analyses will also be performed on the different age and chiropractor strata.

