### Ethics

No serious or lasting side effects have ever been reported in infants following the types of treatment used in this trial and no compensations claims have ever been made for this this age group in Denmark [35]. Because there is no experimental treatment involved, but only treatments, which are usually performed in clinical practice, no interim analyses are made and therefore no data monitoring committee is needed. Furthermore, no standardized treatment in the area exists that the child is withdrawn from.

All parents have given written informed consent for their child to participate in the study and for collection of information from hospital files (Additional file 4). Participation in this study is voluntary, and the parents can withdraw their child from the study at any time with no negative consequences for the child. Parents are advised to immediately contact the chiropractor (who can contact the PI if relevant) if they suspect any serious adverse effect during the project period. In any case of discontinuation, the child’s allocation group will be revealed for the parents. All cases of discontinuations/withdrawals will be registered with reason for withdrawal.

The study has been approved by The Regional Committee on Health Research Ethics (S-2015001), and data are being handled by a data manager at NIKKB according to regulations by the Danish Data Protection Agency. The Regional Committee on Health Research Ethics reviews an annual safety report and any amendments made in the protocol or the documents used in the trial.

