### Trial status

Patient recruitment is ongoing and will continue until 200 participants have been included or approximately  ultimo 2018.

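### The 200 children that give 80% power are an analysed number, but the protocol uses 200 as the number included, which leaves essentially no margin for missing outcomes

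*Protocol article*

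**What the plan says.** The Sample size section starts from a pilot control group whose crying fell by 2.5 h per day. It wants treated children to do one hour better: "children in the intervention group will have a reduction of one additional hour, resulting in a reduction of 3.5 crying hours". The spread is fixed next, "With an assumption of a common standard deviation of 2.5", with "a level of significance on 0.05" and 80% power. The conclusion is that "this result in a sample size of 200 children distributed with 100 in each group". No allowance for loss appears in this derivation.

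The same 200 is then the recruitment target. The Method part of the Abstract gives it as the intended number of children to include. Under Trial status, recruitment "will continue until 200 participants have been included", or until about the end of 2018.

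Statistical analyses names a two-sample t-test on the change in mean daily crying hours, 3–4 days before treatment against 3–4 days after it. Analysis is by intention to treat, and "no data will be imputed". The Ethics section lets parents withdraw at any time and adds: "All cases of discontinuations/withdrawals will be registered with reason for withdrawal".

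**The concern.** Power belongs to the children who enter the test. For this endpoint, a child enters only with diary data from both before and after treatment. If the number needed in the analysis is also the number at which inclusion stops, and missing outcomes are not filled in, every child without an after-treatment diary comes straight off the number that the calculation requires.

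What is at stake is how the result is read. If the trial finds no difference, readers will weigh that against the 80% in the article. If some outcomes are missing, the named test will have had somewhat less than that.

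**Working it through.** **Inputs**
- Difference in mean change: 3.5 − 2.5 = 1.0 h per day (Sample size).
- Common standard deviation of change: 2.5 h (Sample size), so the standardised effect is d = 1.0 / 2.5 = 0.4.
- Significance level 0.05 and power 80% (Sample size). Sidedness is not stated. Two-sided is assumed because it reproduces the stated number; a one-sided test would need only 78 per arm (156 in total).
- Allocation 1:1 (Randomization and blinding).
- Test: two-sample t-test, no imputation (Statistical analyses).
- Loss rate: none given. The values 5%, 10%, 15% and 20% are assumptions, taken as equal in both arms.

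**Step 1: reproduce the stated figure**

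Normal approximation: n per arm = 2 × (1.960 + 0.842)² × 2.5² / 1² = 98.1, rounded up to 99.

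Exact two-sample t-test (noncentral t, d = 0.4): n per arm = 99.08, rounded up to 100, so 200 in total. Power at 100 per arm is 80.4%.

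The plan's figure is reproduced. It is also used up by its own inputs: rounding 99.08 up to 100 is the only slack, so no allowance for loss is contained in it.

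**Step 2: where power crosses 80% (exact t)**

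| Analysed | Power |
|---|---|
| 200 (100 + 100) | 80.4% |
| 199 (100 + 99) | 80.2% |
| 198 (99 + 99) | 79.97% |

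By the normal approximation the crossing comes slightly later: 80.15% at 197 analysed and 79.96% at 196.

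**Step 3: t-test power with 200 included and an assumed loss**

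| Assumed loss | Analysed per arm | Power | Below 80% by |
|---|---|---|---|
| 5% | 95 | 78.3% | 1.7 points |
| 10% | 90 | 76.1% | 3.9 points |
| 15% | 85 | 73.7% | 6.3 points |
| 20% | 80 | 71.0% | 9.0 points |

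**Step 4: the regression already planned**

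Statistical analyses also plans a linear regression of change on baseline crying, randomisation group and stratification factors. Assume equal variances before and after treatment, and let r be the before-after correlation. Adjusting for baseline then reduces the standard deviation of change from 2.5 to 2.5 × √((1 + r)/2). Any gain from the stratification factors is ignored. At 90 analysed per arm (10% loss):

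| Assumed r | Residual SD (h) | d = 1 / SD | Power |
|---|---|---|---|
| 0.3 | 2.016 | 0.496 | 91% |
| 0.5 | 2.165 | 0.462 | 87% |
| 0.7 | 2.305 | 0.434 | 82.5% |
| 0.8 | 2.372 | 0.422 | 80% |

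The article reports no before-after correlation, so each r is an assumption.

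**The case against.** The strongest reply is that nothing is miscalculated. The stated inputs do give 100 per arm, and a journal article may leave an expected loss rate to the full protocol. Both statements are correct, and the lack of a dropout rate is not the point here. What remains rests on figures that the article does state: it attaches 80% power to 200 children, stops inclusion at 200, and fixes a test that uses only observed outcomes.

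Three stronger readings are tempting, and the document supports none of them.
- *Any loss breaks the power claim.* It does not. With one child missing, power is 80.2%; with two it is 79.97%, which is 80% for practical purposes. Up to about 5% loss, the shortfall stays below two points.
- *The protocol expects withdrawals.* It only permits and registers them, which is ordinary ethics wording. Several features favour retention: treatment lasts two weeks, control children are offered free treatment afterwards if symptoms persist, and the pilot found the study length acceptable. Equally, the pilot section reports no retention figure that would justify assuming zero loss, and the Discussion describes parents as often very stressed and two weeks as about the longest they would accept.
- *The trial is too small and must recruit more.* This does not follow. Under the assumptions in the working, the planned regression keeps about 80% power or more at 10% loss for correlations up to 0.8. That regression cannot simply be taken as the primary analysis, though: the article ties the p-value of the main endpoint to the t-test and does not call the regression primary.

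How well the pilot estimates the 2.5 h standard deviation is a separate question that could move power either way. This point does not depend on it.

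**Conclusion.** The point holds as a minor one. The 200 is correctly derived as a number of analysed children and then used as a number of included children, so for the named t-test 80% is close to a no-loss ceiling. The shortfall is negligible for a child or two and becomes material at around 10% loss. The figures rest on the article's own effect and standard deviation, a two-sided test and equal loss in the arms. The true shortfall cannot be known from the article because it gives no loss rate. The alternative end of recruitment by calendar date means that even 200 included is not assured.

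**What to change.** Reword the Sample size section so that 80% power is stated for 100 analysed children per arm. Add the t-test power for 200 randomised at a loss the sponsor considers plausible, for example about 76% at 10%, and label the rate as an assumption.

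Optionally, add the power of the planned baseline-adjusted regression over a range of before-after correlations, with the equal-variance assumption stated. Do not describe that regression as primary unless it is formally designated so.

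The cost is a sentence or two and a slightly less favourable figure for the t-test. Enrolment and the planned analyses stay as they are.
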